**Methods:**

Fifty participants diagnosed with MDD or persistent depressive disorder (PDD) will be recruited from a tertiary mood disorders clinic and undergo 1:1 randomization into either an experimental or control arm. Participants will be given either 25 mg psilocybin or 25 mg microcrystalline cellulose (MCC) placebo for the first treatment. Three weeks later, those in the control arm will transition to receiving 25 mg psilocybin. We will investigate whether treatments are associated with changes in arterial spin labelling and blood oxygenation level-dependent contrast neuroimaging assessments at acute and subacute timepoints. Primary outcomes include testing whether psilocybin demonstrates acute changes in (1) cerebral blood flow and (2) functional brain activity in networks associated with mood regulation and depression when compared to placebo, along with changes in MADRS score over time compared to placebo. Secondary outcomes include changes across complementary clinical psychiatric, cognitive, and functional scales from baseline to final follow-up. Serum peripheral neurotrophic and inflammatory biomarkers will be collected at baseline and follow-up to examine relationships with clinical response, and neuroimaging measures.

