### Objectives {7}

Our primary objective is to test whether psilocybin (prior to adjunctive psychotherapy) leads to significant acute and subacute changes in functional brain activity in networks associated with mood regulation and depression compared to placebo and supportive therapy. We hypothesize that regional CBF will be modulated during the acute phase of treatment relative to placebo, particularly in brain networks associated with mood regulation and depression. Specifically, there will be an acute increase in dorsolateral prefrontal cortex blood flow and a reduction in the subgenual anterior cingulate cortex blood flow between baseline and the first active treatment (Treatment Visit 1). The CBF findings will be contrasted against resting-state fMRI data. Our secondary objective is to examine whether participants treated with psilocybin-assisted psychotherapy will have a greater reduction in depression scores over time signified by the MADRS relative to those who receive placebo. Our secondary hypothesis is that a reduction in MADRS score will be related to an increase in dorsolateral prefrontal cortex blood flow and a decrease in subgenual anterior cingulate cortex blood flow between baseline and the first treatment visit among participants treated with psilocybin compared to placebo. Additionally, our exploratory objective will examine blood biomarkers that are mechanistically related to psilocybin and/or MDD including those involved with increased neurogenesis and neuroplasticity (BDNF), glial pathology (S100B), and systemic inflammation (CRP). It is predicted that these biomarkers will be associated with MADRS scores at baseline. Our exploratory hypothesis is that our baseline blood-based biomarkers of interest will predict treatment response (i.e., changes in depression scores) measured over time by the MADRS. It is expected that there will be a post-treatment increase in BDNF and a reduction in CRP and S100B plasma levels.

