### Trial design {8}

EMBRACE is a randomized, placebo-controlled, delayed-start trial that investigates neuroimaging, blood biomarkers, and clinical changes associated with psilocybin therapy in those with a unipolar depressive disorder. The protocol is documented as adhering to the SPIRIT checklist [see Additional file 1]. For the purposes of this study, a depressive disorder will include MDD or persistent depressive disorder (PDD) as indicated by the Mini-International Neuropsychiatric Interview (MINI) with a current major depressive episode as defined by the DSM-5.0 and confirmed by an interventional psychiatrist [75]. Study assessments/visits will occur at intervals that are reported in Fig. 2. This study aims to recruit and treat up to 50 participants at Sunnybrook Health Sciences Centre, University of Toronto, Toronto, Ontario, Canada. Participants will be screened by a study coordinator to determine study eligibility, and if eligible will undergo a baseline assessment, preparatory supportive psychotherapy, and neuroimaging 1 week prior to randomization. At the first treatment session (Treatment Visit 1), participants will be randomized to either group 1 or group 2. Participants in group 1 will receive a high dose of synthetic psilocybin (25 mg) while in group 2 will receive inert placebo (25 mg MCC). Three weeks later (Treatment Visit 2), participants in group 1 and group 2 will both receive a high dose of synthetic psilocybin (25 mg). This delayed-start design allows for the comparison of outcomes between the two groups while also evaluating the effect of the intervention over time. At each Treatment Visit, all participants will undergo neuroimaging after dosing, and two qualified staff members will observe and provide supportive psychotherapeutic support for approximately 8 h post-treatment administration. A diagram of the study design and stages is presented in Fig. 1.

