## Assignment of interventions: allocation

### Sequence generation {16a}

Participants will be randomized with a computer-generated 1:1 randomized allocation into either the psilocybin or placebo group for dosing visit 1 by an independent external assistant using REDCap Randomization Module. Each participant will have an equal probability of being added to either group. Group sizes will be fixed, and study personnel will be blind to randomized allocation. A flowchart for participant randomization is provided [see Additional file 5]. All participants will receive open-label psilocybin at the second treatment visit.

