## Data collection and management

### Plans for assessment and collection of outcomes {18a}

The assessments to be collected for both primary and secondary outcomes can be found in Table 2. For each participant, much of the data will be securely stored in the form of an electronic case report form (eCRF) which will include participant demographics, clinical scales and assessments, medical information including any pre-existing conditions and history, concomitant medications and therapies, vital signs (i.e., ECG, blood pressure), baseline blood tests, follow-up visits, any AEs or SAEs (if applicable), documentation of a participant’s informed consent, study visit dates, participant identification numbers, and any documentation pertaining to the appropriate data entry, management, validation, and archival. Paper-based copies of study questionnaires will be kept in the physical CRF with the unique, anonymized identification number assigned to a given participant and securely stored on-site in an area with restricted access at the hospital. Participant data captured during the trial will only be identified by a participant ID and managed in the electronic CRF (eCRF) that will be securely stored in online Research Electronic Data Capture (REDCap) software. REDCap is a secure, web-based software that is designed to support data capture for clinical trials and research studies. MRI data will be stored on a secure research server at Sunnybrook Health Sciences Centre. All questionnaires used in the study have been previously published and validated for research and/or clinical use. The ASL and MRI techniques have been previously published and validated.

**Table 2 Tab2:** Primary and secondary outcomes

**Primary outcomes**	• Significant alterations in regional CBF across three a priori brain regions from baseline to treatment visit 1
	• Improvement in depressive symptoms using the Montgomery-Asberg Depression Rating Scale (MADRS) from baseline to week 3 and week 6 following initial psilocybin/placebo administration. Higher scores with respect to the MADRS minimum (0) and maximum (60) values represent a worse treatment outcome [89]

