**Secondary outcomes**	• Baseline grid-version of the 17-item Hamilton Depression Rating Scale (GRID-HAMD-17) score [Time Frame: Baseline]. The GRID-HAMD is a 17-item clinician-administered rating scale designed to assess severity of depressive symptoms. The score range is 0 to 52, with higher score indicating more severe depression [90]
	• Incidence of response [Time Frame: Up to study end point]. The proportion of participants with a response (defined as a ≥ 50% improvement in MADRS total score from Baseline) at week 3 post psilocybin administration. The minimum and maximum values are 0 and 60 and a higher score represents a worse outcome [91]
	• Incidence of remission [Time Frame: study endpoint]. The proportion of participants with remission (defined as MADRS total score < 11) at week 3 and 6 following the initial psilocybin/placebo administration. The minimum and maximum values are 0 and 60 and a higher score means a worse outcome [91, 92]
	• Patient Health Questionnaire 9-item (PHQ-9) [Time Frame: Baseline up to study end point/weeks]. The PHQ-9 is a self-rated measure of depressive symptom severity in the past two weeks. Each of the nine items is rated on a Likert scale, ranging from 0 (not at all) to 3 (nearly every day), and summed for a total score between 0 (no symptoms) to 27 (most severe) [93]
	• 16-item Quick Inventory of Depressive Symptomatology–Self-Report (QIDS-SR-16) [Time Frame: Baseline up to study end point/weeks]. The QIDS-SR-16 is a self-report scale with scores that range from 0 to 27. Higher scores indicate greater depression [94]
	• Clinical Global Impressions Scale (CGI) [Time Frame: Baseline up to study end point/weeks]. The CGI severity module assesses the severity of a person’s depressive illness using a seven-point Likert scale, ranging from “Normal, not at all depressed” to “Among the most extremely depressed patients”. The CGI improvement module evaluates the global improvement of a person’s condition since their last visit on a seven-point Likert scale, ranging from “Very much improved” to “Very much worse” [95]

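### MADRS at week 6 is part of a primary outcome compared with placebo, but both arms have received open-label psilocybin by then; only week 3 supports a placebo comparison

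*Protocol article*

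**What the plan says.** - **Time points.** Table 2, under {18a}, lists as its second primary outcome the improvement in MADRS "from baseline to week 3 and week 6 following initial psilocybin/placebo administration". The statistical methods section {20a} names MADRS at baseline, week 3 and week 6 in its sentence on the primary mixed-effects analysis.
- **Comparator.** The Methods paragraph of the Abstract, in the sentence that lists the primary outcomes, adds MADRS with the words "along with changes in MADRS score over time compared to placebo". Objectives {7} treats MADRS as a secondary objective, also against placebo: participants given psilocybin "will have a greater reduction in depression scores over time signified by the MADRS relative to those who receive placebo".
- **Treatment at week 3.** Trial design {8} says: "Three weeks later (Treatment Visit 2), participants in group 1 and group 2 will both receive a high dose of synthetic psilocybin". Sequence generation {16a} adds: "All participants will receive open-label psilocybin at the second treatment visit". Participant timeline {13} also calls the second treatment open-label.
- **Stated purpose of the design.** Trial design {8}: "This delayed-start design allows for the comparison of outcomes between the two groups while also evaluating the effect of the intervention over time".
- **Response and remission.** In Table 2, response is assessed "at week 3 post psilocybin administration". The next row, remission, is counted at weeks 3 and 6 from the first psilocybin or placebo administration.

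**The concern.** The time points, the comparator and the week-3 dosing cannot all stand together. A placebo comparison needs a group that has had only placebo, and at week 6 there is none. Nothing in the article limits the placebo comparison to week 3 or gives the week-6 contrast another name.

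What is at stake is the reading of a primary outcome in a trial whose Discussion hopes to establish efficacy. If psilocybin works and the controls improve after their own dose, a small week-6 difference could be taken as loss of effect. If a difference remains at week 6, it reflects the number and timing of doses under open-label conditions, yet it would be reported under a primary outcome described as compared with placebo.

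The response outcome has a separate, smaller inconsistency. Its clock starts at psilocybin, so the two arms are read at different study weeks.

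**Working it through.** The document gives no MADRS effect size, SD or power (Sample size {14} says that no power analysis was done for this hypothesis), so there is no MADRS figure to reproduce. The check is of exposure by visit, followed by an illustration on assumed values.

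**1. Exposure by visit.** Intervention description {11a} puts the first treatment on day 14.
- Second treatment, three weeks later: 14 + 21 = day 35, which is week 3.
- Week 6: 14 + 42 = day 56, which is 56 − 35 = 21 days after the second treatment.

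| Time after first treatment | Group 1 (n = 25) | Group 2 (n = 25) | Between-arm contrast |
|---|---|---|---|
| Week 3, before second treatment | psilocybin | placebo | psilocybin versus placebo |
| Week 6 | psilocybin, then psilocybin | placebo, then psilocybin | immediate versus delayed start |

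Participants on placebo alone at week 6, by design: 0 of 50. The last-observation rule in {20c} could bring a placebo-period score forward for a control who left before the second treatment. That would mix exposures within the arm and would not create a placebo group.

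**2. What the week-6 contrast estimates.** Write A for the benefit in group 1 at week 6 relative to no active drug, and C for the benefit in group 2 from its single dose three weeks earlier. The between-arm difference is A − C, whereas a placebo comparison would give A. The two differ by C, so the contrast understates the drug effect by whatever the control arm gains from its own dose.

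**3. Does the model help?** Equation 1 in {14} has Drug and Drug-by-Visit terms and is specified for CBF. Suppose the same form is used for MADRS. If Drug means the drug last taken, there is no placebo cell at week 6. If Drug means the randomised arm, the week-6 term is A − C. Neither is psilocybin versus placebo.

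**4. Illustration (all MADRS values assumed).** With n = 25 per arm and two-sided 0.05, power ≈ Φ(δ / (SD × √(2/25)) − 1.96). For a week-3 difference of 6 and SD 12: 6 / (12 × 0.2828) = 1.768, and Φ(1.768 − 1.96) = 0.42. For 10 and SD 8: 10 / (8 × 0.2828) = 4.42, and Φ(4.42 − 1.96) = 0.99.

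| Share of the week-3 difference left | Power, lowest to highest (difference 6 to 10, SD 12 to 8) |
|---|---|
| All (the week-3 contrast itself) | 42% to 99% |
| Half, at week 6 | 14% to 60% |
| A quarter, at week 6 | 6.5% to 20% |
| None, at week 6 (full catch-up) | 5%, the type I error |

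**5. Response anchor.** Counted literally, three weeks after psilocybin is day 35 + 21 = day 56 (week 6) for group 2, because its only psilocybin dose is on day 35. For group 1 it is day 14 + 21 = day 35 (week 3) if counted from its first dose. Remission is read at the same study week in both arms.

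**The case against.** The strongest defence has four parts.

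- **No single sentence claims psilocybin against placebo at week 6.** The Table 2 row names no comparator; there, psilocybin/placebo only dates the visit. The Abstract and the Objectives say over time and name no week. This is correct, and a reader who infers an express week-6 placebo claim goes further than the text. The conflict comes from joining the Table 2 time points to the Abstract's comparator for the same primary outcome, with nothing to separate them.
- **The design is openly delayed-start.** Trial design {8} announces a comparison of the two groups, and the Discussion lists cumulative treatment effects as an aim. This stands as a reason to collect and report week 6. The contrast is still randomised, so it need not be dropped or reduced to description. It does not make the contrast placebo-controlled.
- **The main endpoint is untouched.** Sections {14} and {20a} define the sized primary endpoint as the CBF contrast at Treatment Visit 1, before anyone has a second dose, and Objectives {7} places MADRS second. This limits the reach of the point. Table 2 and the Abstract nevertheless label MADRS primary.
- **The exact MADRS contrast may be in an analysis plan.** It may, but no analysis plan can supply a placebo group at week 6.

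Two other inferences should be resisted. One is that weeks 3 and 6 will be averaged, which under full catch-up would halve a 6-point difference to (6 + 0) / 2 = 3; no passage plans to average them. The other is that the response definition removes the randomised placebo comparison altogether; MADRS change and remission at week 3 both keep it.

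**Conclusion.** The point holds as an inconsistency in what a primary outcome estimates. The week-3 MADRS difference, rated before the second treatment, is the only randomised placebo comparison of MADRS among the two primary time points. The week-6 difference is an immediate- versus delayed-start contrast, open-label after week 3, in which the arms differ in number of doses and in time since first active dose.

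That there is no placebo-only group at week 6 follows from the document alone. The size of the shrinkage does not: it depends on how far the control arm responds to its own dose. A reader might infer that the week-6 difference must be zero, but that needs full catch-up and no added benefit from the earlier or second dose, neither of which the document states. The power figures rest on the assumed differences and SDs and are illustrations only. Whether MADRS is adequately powered at week 3 is a separate question that this correction does not settle.

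The response anchor is a lesser, separate inconsistency in a secondary outcome. The CBF primary endpoint is not affected.

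**What to change.** 1. In the Abstract, Table 2 and {20a}, state that the placebo-controlled primary MADRS contrast is the between-arm difference in change from baseline to week 3, rated before the Treatment Visit 2 dose.
2. Take week 6 out of the placebo-controlled primary outcome. Report it as a secondary randomised comparison of immediate with delayed start: two psilocybin doses versus placebo then one dose, open-label after week 3.
3. Anchor response to week 3 after the first psilocybin or placebo administration, as remission already is. Give week-6 response and remission the same immediate- versus delayed-start label.

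The cost is wording in those places, with no new data, visits or participants. The sponsor gives up only a placebo-controlled reading of week 6, which the design cannot provide. The change should be made before any unblinded MADRS data are seen.

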### Plans to promote participant retention and complete follow-up {18b}

Participants will be compensated for their commitment to all evaluations and training sessions in the form of $75 CAD per session until their final follow-up that indicates their last session.

### Data management {19}

Any data collected in this study by appropriate study personnel, including those involved in data entry, will be recorded as source documents, and further entered into both paper and electronic case report forms in an anonymized manner. Any essential documents will be collected and stored in the Trial Master File for this study in accordance with Division 5 Regulations and ICH GCP E6. Storage of data will be centrally stored and managed by the Centre for Clinical Trial Support at SHSC. Contemporaneous review of the laboratory results and the assessment of clinical significance for those results considered out of range will be documented by means of dated signature by the reviewing investigator. Those who are given authorization to access the data will be determined by the study investigators. The investigators will review individual study participant records and append a signature where appropriate to ensure that data is accurate, complete, and secure.

### Confidentiality {27}

Confidentiality will be maintained for all potential and enrolled participants in accordance with the requirements stipulated by the Canadian Personal Health Information Protection Act of 2004 (PHIPA) and the Sunnybrook Health Sciences Centre Research Ethics Board (REB). Any personal information collected and stored in paper-based files will be kept in a secure area within SHSC; however, many of the eCRFs will be stored in a secure REDCap web-based application.

### Plans for collection, laboratory evaluation, and storage of biological specimens for genetic or molecular analysis in this trial/future use {33}

Baseline blood-based biomarkers that are mechanistically related to psilocybin and/or MDD will be collected, made optional in the consent form, and will be investigated for potential association with MADRS scores at baseline. Peripheral biomarker levels will be evaluated for associations with treatment response (changes in MADRS scores) over time. Blood plasma and serum samples will be stored and batched on-site and in the appropriate − 80 °C freezer at SHSC for future analysis.

## Statistical methods

### Statistical methods for primary and secondary outcomes {20a}

The primary and secondary analyses will be conducted at Sunnybrook Health Sciences Centre, using open-source software tools, to the extent it is possible. Image processing will be conducted by a trained individual who will remain blind to the treatment allocation throughout the data analysis period. We propose to analyze our primary outcome using mixed-effects linear regression to measure CBF changes across our regions of interest from Baseline to Treatment Visit 1, as well as MADRS changes from Baseline, Week 3, and Week 6 following administration. A priori CBF regions consist of emotion regulation regions that are disrupted in MDD [109, 110], comprising the dorsolateral prefrontal cortex, salience network regions comprising the insula cortex, and default mode network comprising the parietal precuneus.

We will determine an optimal model for data analysis by fitting the model described in Eq. 1 to data using the *lme4* package in R, as well as additional models adding interaction effects of age, sex, and number of prior failed antidepressant treatments with drug to assess whether demographics or treatment-resistance modify the effect of psilocybin. An optimal model will be selected by comparing models fit by maximum likelihood estimation using a chi-squared test of model deviance. This will provide the added benefit of further robustness against the possibility of model non-convergence. As described in the sample size calculation, marginal means of a Visit x Drug interaction will be estimated using the *emmeans* package in R, and two within-subject contrasts of baseline to treatment visit 1 change in CBF will be calculated as well as a between-subject difference in these contrasts. Sidak’s correction for multiple comparisons will be applied to adjust *p*-values, with the primary outcome measure being the between-subject difference in the change in CBF attributable to psilocybin vs placebo at treatment visit 1.

For our exploratory analysis, peripheral levels of S100B, BDNF, and CRP will be measured using standard enzyme-linked immunosorbent assays or similar multiplexed immunoassay. All data analyses will be performed using SPSS 22.0. Multivariate linear regression analysis will be used to assess the relationship between baseline and change in peripheral biomarker measures and post-treatment change in MADRS scores.

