
### Sample size {14}

As this study will employ a longitudinal design with multiple visits where CBF measurements in individual subjects may reasonably be expected to be highly dependent across visits, we will model use linear mixed-effects models of CBF at all visits to account for effects of psilocybin and MCC placebo independently of baseline CBF. Specifically, we will use the following model (in *lme4* syntax):1$$CBF\sim Age+Sex+Drug+Drug\;x\;Visit+(\mathit1\;\vert\;ID)$$

To assess the difference in CBF associated with psilocybin relative to placebo, marginal means of a Visit x Drug interaction will be calculated using the *emmeans* package in R, and contrasts between baseline and treatment visit 1 CBF under psilocybin and placebo conditions will be calculated separately, and an additional contrast composed of the difference of these two contrasts will be calculated. Sidak’s correction for multiple comparisons will be used to adjust *p* values. The primary endpoint will be the contrast estimating the between-group difference in within-subject differences in psilocybin- and placebo-induced CBF changes at treatment visit 1 vs baseline (i.e. [V1 psilocybin − V0] − [V1 placebo − V0]).

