As a power analysis, we simulate 500 datasets each for groups of size *N* = 5 − 50, in increments of 5. For each simulated subject, baseline CBF is sampled from a normal distribution 55 ± 13 mL/100/g min. At each subsequent visit, a ± 3% test-retest variability is added to the baseline CBF. At psilocybin visits, relative to subject-specific baseline CBF, a proportional 23% ± 23% increase in CBF is added. MCC placebo has no direct psychotropic effects. For each of these 500 datasets, a model (Eq. 1) is fit to the data, and the contrasts described above are calculated. Sufficient power is achieved when evaluation of the between-group contrast of interest for a given group size produce corrected *p*-values below *α* = 0.05 at a frequency equal to or greater than a pre-specified power of 80%. This power analysis suggests two groups of *N* = 20 are sufficient to reject the null hypothesis in > 80% of cases. Sensitivity analyses additionally suggest that sufficient power can be achieved with *N* = 25 in each group if test-retest variability is as high as 7.5%, or if psilocybin effect size and variance is scaled from 23% to as low as 15% [see Additional file 3]. As these simulated datasets are likely somewhat idealized relative to real-world data, we will use a total of *N* = 50 subjects with 25 allocated to each arm.

These anticipated CBF group session differences are consistent with a recently conducted acute neuroimaging clinical trial in bipolar depression [82]. Although we do not conduct a power analysis for H_A,2_, we provide context from the literature in support of the MADRS outcome measure. Example studies incorporating the MADRS outcome measure are provided [see Additional file 4], showing trial design, sample sizes, intervention details, and the reported changes in MADRS score [83–87].

Thus, our MADRS assessments for *N* = 50 is consistent with previous depression trials and support our second hypothesis (H_A.2_).

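### If Eq. 1 is carried over to MADRS by randomised arm, the week-3 comparison is an unadjusted change-score difference; baseline adjustment costs almost nothing and may gain precision

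*Protocol article*

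**What the plan says.** Table 2 of the protocol article lists as a primary outcome "Improvement in depressive symptoms using the Montgomery-Asberg Depression Rating Scale (MADRS) from baseline to week 3 and week 6 following initial psilocybin/placebo administration". (The Objectives section places the MADRS comparison under the secondary objective; that is a separate matter.) The section Statistical methods for primary and secondary outcomes {20a} names mixed-effects linear regression for CBF changes "as well as MADRS changes from Baseline, Week 3, and Week 6 following administration". No MADRS equation, contrast or baseline term follows.

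The next paragraph of {20a} begins "We will determine an optimal model for data analysis by fitting the model described in Eq. 1 to data using the" lme4 package. The candidate extensions it lists are interactions of drug with age, sex and number of prior failed antidepressant treatments, chosen between by deviance tests. None brings in baseline.

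Eq. 1, in Sample size {14}, has CBF at all visits as the response. Its terms are age, sex, a `Drug` main effect, a `Drug`-by-`Visit` interaction and a random intercept per participant. Its purpose is stated as "to account for effects of psilocybin and MCC placebo independently of baseline CBF". The contrast taken from it is the "contrast estimating the between-group difference in within-subject differences in psilocybin- and placebo-induced CBF changes at treatment visit 1 vs baseline". The same section plans 25 participants per arm and says that no power analysis was done for the MADRS hypothesis.

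**The concern.** In a model of this form the baseline value is one of the responses. If `Drug` is the randomised arm, each arm gets its own baseline mean, and any chance difference between those means is subtracted in full from the follow-up difference. Randomisation says the two arms share one baseline mean. A model that uses this fact subtracts only the part of the baseline difference that the correlation supports.

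What is at stake is precision. MADRS is a listed primary outcome with 25 per arm and no power calculation, so avoidable variance matters more here than for CBF. The stated model selection cannot repair this, because no candidate model contains a baseline adjustment. The issue mainly concerns week 3: at Treatment Visit 2, three weeks after the first dose, both arms receive psilocybin, so week 6 no longer compares psilocybin with placebo.

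**Working it through.** **The plan's own figure.** There is none for MADRS. The only power statement, N = 20 per group for more than 80%, is for CBF and is not an input here. Simulated from its stated inputs, it gave 90.6% to 95.8% in three of four readings of the setup and 77.4% in the fourth.

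**Inputs.** From the protocol: 25 per arm, 1:1 allocation. Assumed, because the protocol gives none: baseline SD s0, follow-up SD s1 and their correlation r. Table 1 requires HAMD-17 above 17 at entry, which may make s0 smaller than s1, so unequal SDs are included.

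**Step 1: what Eq. 1 estimates.** With arm coding and complete data, the interaction contrast is (mean change, arm 1) − (mean change, arm 2). In 300 simulated trials (25 per arm, three visits, SD 8, correlation 0.5), the fitted contrast and the plain change-score difference differed by less than 2 × 10⁻¹³.

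**Step 2: variances per participant.**
- Change score: s0² + s1² − 2·r·s0·s1
- Baseline-adjusted, large sample: s1²·(1 − r²)
- Difference: s0² − 2·r·s0·s1 + r²·s1² = (s0 − r·s1)²

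The difference is a square, so adjustment never loses asymptotically. It gains nothing exactly when r = s0/s1. With s0 = s1 the ratio of adjusted to change variance is (1 + r)/2.

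**Step 3: numbers.** Detectable difference = 2.83·√(2·Var/25), where 2.83 is a rounded multiplier for two-sided 5% and 80% power (normal quantiles give 1.96 + 0.84 = 2.80; a t-test needs slightly more).

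| s0 / s1 | r | Var change | Var adjusted | Ratio | Detectable, change → adjusted |
|---|---|---|---|---|---|
| 8 / 8 | 0.3 | 89.6 | 58.24 | 0.65 | 7.6 → 6.1 |
| 8 / 8 | 0.5 | 64 | 48 | 0.75 | 6.4 → 5.5 |
| 8 / 10 | 0.3 | 116 | 91 | 0.78 | 8.6 → 7.6 |
| 8 / 10 | 0.5 | 84 | 75 | 0.89 | 7.3 → 6.9 |
| 6 / 9 | 0.3 | 84.6 | 73.71 | 0.87 | 7.4 → 6.9 |
| 6 / 9 | 0.5 | 63 | 60.75 | 0.96 | 6.4 → 6.2 |
| 0.75 / 1 | 0.7 | 0.5125 | 0.51 | 0.995 | – |
| 0.5 / 1 | 0.5 | 0.75 | 0.75 | 1.00 | – |

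Worked example (8 / 10, r = 0.3): 64 + 100 − 48 = 116; 100 × 0.91 = 91; 91/116 = 0.78; 2.83·√(2·116/25) = 8.6 and 2.83·√(2·91/25) = 7.6.

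With equal SDs, a change-score analysis needs 50/0.65 ≈ 77 or 50/0.75 ≈ 67 participants to match 50 with adjustment. At r = 0.5 and equal SDs, power for a difference of 0.6 SD is 56% unadjusted against 69% adjusted; for 0.8 SD it is 81% against 90%.

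**Step 4: simulation check.** In the same 300 trials, constraining a common baseline mean cut the model-based variance to 0.754 of its value (theory 0.75). The empirical variance of the estimate fell from 4.59 to 3.29, and to 3.36 with baseline as a covariate.

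**The case against.** The strongest objection is that the document never writes a MADRS model. Eq. 1 has CBF as its response, the contrasts described in {20a} are CBF contrasts, and the MADRS clause lists time points without saying how baseline enters. A reader might infer that the protocol prescribes separate baseline means for the arms on MADRS. It does not; that is an inference from the only model on offer. This objection stands and limits how the point may be put. What remains is that the approach given, including its candidate extensions, contains no route to baseline adjustment.

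Second, `Drug` is not defined. The contrast in {14} writes V0 without an arm label. If `Drug` meant the drug received at the visit, with none at baseline, the arms would already share a baseline mean, and the fix would be in place. Against this, {14} takes `Visit`-by-`Drug` marginal means and computes baseline-to-visit-1 changes separately for psilocybin and placebo. That calls for a baseline cell at each `Drug` level, and neither drug has been given at baseline. Arm coding is therefore the more natural reading, but it is not stated.

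Third, the gain is assumption-driven. This also stands: equal SDs give the most favourable figures, and the entry threshold on HAMD-17 argues for a narrower baseline spread and a smaller gain. Nothing in the document says what correlation to expect.

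**Conclusion.** The point holds as a conditional one about efficiency. If Eq. 1 is applied to MADRS with `Drug` as arm, the week-3 contrast is the unadjusted change-score difference, and baseline adjustment is asymptotically at least as precise. Under the assumed values the variance saving is 25–35% (equal SDs, correlation 0.3–0.5), 11–22% (SDs 8 and 10), 4–13% (SDs 6 and 9), and close to nil when the correlation is near the ratio of baseline to follow-up SD. No single figure can be attached to this trial.

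Two stronger readings are not supported. One is that the MADRS result would be biased or its type I error wrong: under randomisation the change-score contrast is unbiased. The other is that the same argument applies with force to CBF: under the protocol's own CBF simulation inputs the gain was put at only about 1–3%, so CBF lends the MADRS point no support.

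**What to change.** Write the MADRS model explicitly. State that the week-3 between-arm difference is estimated either with baseline MADRS as a covariate, or with a repeated-measures model that constrains the arms to a common baseline mean (no arm effect at baseline, arm effects at later visits only). Define `Drug` as randomised arm or as drug received at the visit, so that the handling of baseline can be read from the model.

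The cost is wording only, plus about one degree of freedom for the covariate. No new data are needed, because the outcome is already defined from baseline MADRS. Fixing this before unblinding also removes a later choice between adjusted and unadjusted results, which can differ when 50 participants show a chance baseline imbalance.
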